### Data Management and Monitoring

Owing to the minimal risks associated with study participation, it is not necessary to implement an independent data and safety monitoring board. The research team will be responsible for monitoring and data management and will meet regularly to manage the protocol, monitor recruitment, and deal with any adverse events. The reporting of this study will be conducted according to the CONSORT (Consolidated Standards of Reporting Trials) statement guidelines [79].

All data will be collected via the web using Qualtrics (Provo) for survey responses and Inquisit 6.4 for task data and self-reported engagement responses, and temporarily stored on these servers. Data safety and security measures have been considered, including restricted access to the research team, password protection, firewall, and virus protection. Furthermore, each participant will be assigned a unique participant code (blinded to the group the participant has been assigned to) and will be asked to self-generate an ID code (instead of participants’ personal information). Thus, this coded data may be reidentifiable during the research but will be deidentified upon completion of the study. An electronic, password-locked master file will be created that matches the unique participant code to their self-generated code to ensure participants are allocated to the correct experimental group and that the survey and task data match across the different time points. All data will be stored on a secure password-protected university server and accessed only by the research team. Upon completion of the project, electronic research data will be deposited in the university’s research data storage system and retained for a minimum of 15 years. The final coding scheme for outcome measures will be available from the authors upon request.

On the basis of previous similar trials, no adverse events are expected [10]. A small amount of fatigue and some mild discomfort during the training task may be experienced. This will be managed by providing participants with enough rest periods between blocks of trials. If the research team becomes aware of any harm or other adverse events, it will be documented and reported appropriately. The research team will also manage any risks and recommend participants to liaise with relevant services, such as psychological assistance, if appropriate. The study will be stopped if evidence emerges that participants can come to harm because of the ABMT intervention.

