### Randomization, Allocation Concealment, and Blinding

Participants fulfilling eligibility criteria and willing to participate in this study will be randomly allocated to 1 of the 3 training conditions after the baseline assessment. Randomization will be performed before participants are enrolled by an independent person blinded to all processes within the intervention, using a computerized random number generator. A block randomization technique will be used, allowing 6 participants at a time to be randomized in equal proportions to the 3 training arms. The allocation numbers will be stored on a password-protected university database maintained by the same independent person and will be revealed after participants are enrolled and baseline assessments are completed.

Each time a participant completes the baseline survey, an automatic email will be sent to the principal researcher ([name]). After receiving this email, the participant will be allocated to the next number on the list and, consequently, be assigned to a training arm. Researchers and participants will be blinded to group allocation throughout the trial (ie, double-blind study design). Furthermore, as assessments and training will occur on the web, in the absence of the investigators, the outcome data will be blinded. However, it is possible that a researcher could become aware of the participants’ training conditions to support them adequately in the instance of technical problems. However, it is unlikely that this will entail problems of bias allocation or assessment because of the web-based nature of the study.

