### Procedure

After informed consent is obtained and participants are eligible, they will complete the web-based baseline assessment (approximately 35 minutes) containing demographic questions as well as questions relating to their general health, current mental health, pain experience, and everyday thoughts and behaviors. At the end of the survey, participants will select their preferred days for training, which will be either (1) Monday and Thursday or (2) Tuesday and Friday. Participants will also be asked to provide an email address so that the research team can send links to the training sessions. Participants will then be randomized into 1 of the 3 groups and be invited by email to start their first training session. This email will include a weblink to the appropriate version of the intervention, as well as instructions on how to download the program.

Training sessions will be performed on the web at the participants’ time and place of convenience (using their own computers), twice a week on a separate pair of days (Monday and Thursday or Tuesday and Friday) for 3 consecutive weeks, totaling 6 sessions. This dosage is based on previous pain ABMT literature, which has shown positive training effects for dosages ranging between 4 and 8 sessions [4,7,8]. It is anticipated that the first and final sessions will take approximately 30 minutes, as it includes cognitive assessment measures, whereas sessions 2 to 5 will take approximately 15 minutes to complete. Participants will be asked to complete the sessions during normal waking hours and within 24 hours of receiving a web link. Each session will start with the same instructions, similar to those of previous research [10], and highlight the need to create a quiet and private environment free from distractions for at least 30 minutes. In total, the participants will be sent 6 session links. Necessary reminders will be sent via email and SMS text messages throughout the study.

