### Outcomes and Measures

#### Overview

Tasks will be presented using Inquisit 6.4 on participants’ internet-connected computers, and questionnaires will be administered using the web-based system Qualtrics (Provo), except for self-reported engagement, which will be administered using Inquisit 6.4. Assessments for all training conditions will be conducted at baseline, during training, immediately after training, and at the 1-month follow-up. A list of all outcomes, measurement instruments, and corresponding time points is presented in Table 1.

**Table 1 table1:** Study outcome measures by assessment time point.

Outcome and variable		Measure	Assessment time point			
			Baseline	During training	Posttraining	1-month follow-up

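### Adverse events are recorded if the team happens to hear of them, and no instrument asks about unwanted effects, so effects other than lasting symptom change will probably be under-recorded (low priority)

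*Protocol article*

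**What the plan says.** All of the safety text is in the Protocol article under Data Management and Monitoring. The capture rule is conditional: "If the research team becomes aware of any harm or other adverse events, it will be documented and reported appropriately". The article expects no adverse events, on the strength of earlier similar trials, but then adds: "A small amount of fatigue and some mild discomfort during the training task may be experienced". It manages these with rest periods between blocks.

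Two commitments depend on harm being noticed. The research team "will meet regularly to manage the protocol, monitor recruitment, and deal with any adverse events", and "The study will be stopped if evidence emerges that participants can come to harm because of the ABMT intervention". There is no independent monitoring board, because the risk is judged minimal.

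On contact with participants, Randomization, Allocation Concealment, and Blinding describes the setting: "as assessments and training will occur on the web, in the absence of the investigators". On what is measured, Outcomes and Measures (Overview) says: "A list of all outcomes, measurement instruments, and corresponding time points is presented in Table 1".

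**The concern.** In a trial with clinic visits, a rule that depends on the team becoming aware of an event is partly made good by staff who see and talk to participants. Here no visit exists. Unless a survey asks, an unwanted effect reaches the team only if the participant decides to write in.

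What is at stake is limited. The adverse-event count at the end would be hard to interpret: a low or zero count could mean that little happened or that little was volunteered. In the meantime, the team's meetings and its undertaking to stop for harm would have little systematic information to work from. The efficacy comparisons are untouched.

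**Working it through.** The plan gives no figure on this point to reproduce. The check is a count of Table 1, a comparison of the relevant text, and one illustration with assumed inputs.

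**1. Rows of Table 1.** Eligibility and demographics 2, pain experience 2, pain intensity and interference 2, self-reported engagement 2, behavioural engagement 2, secondary outcomes 5, additional measures 6. Total: 2 + 2 + 2 + 2 + 2 + 5 + 6 = 21.

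**2. Rows collected once training has begun** (a tick during training, at posttraining or at 1 month). Pain 2, self-reported engagement 2, behavioural engagement 2, secondary 5, additional 4 (attentional control, pain treatment, validity check, manipulation check). Total: 2 + 2 + 2 + 5 + 4 = 15.

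**3. What those 15 rows can show about harm.**
- Asking about unwanted effects: 0 of 15.
- Able to show worsening or changed care: 6 of 15 (the four PROMIS forms, the PGIC and the pain-treatment question).
- Indirect evidence on tolerability: 2 of 15 (attrition and completion).
- The other 15 − 6 − 2 = 7 (two engagement ratings, attentional bias, interpretation bias, attentional control, validity check, manipulation check) do not bear on harm.

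**4. Questions around the sessions.** Procedure has participants rate their experience after each session. The Engagement section and Table 1 show this to be a single item on how engaging the session was. Fatigue and discomfort during the task therefore have no item, either at the session or later.

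**5. Who receives the posttraining survey.** Procedure ties the invitation to completing the final training session, whereas it sends the 1-month survey to everyone. Statistical Methods (Overview) intends to follow up all randomised participants, including those who withdraw. Read literally, a person who stops because training was unpleasant is not asked anything until the 1-month survey. For scale, Sample Size Estimation expects about 30% dropout, or 0.30 × 120 = 36 people. The article does not say how many of these would stop during training rather than miss a later survey, so 36 is not a count of people missed.

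**6. Illustration only.** Let p be the true proportion with an unwanted effect and c the chance that it gets recorded. Both are assumptions; the document gives neither. With n = 40 per arm, expected records = n·p·c and P(none recorded in an arm) = (1 − p·c)^40. For p = 10% (4.0 affected per arm):
- c = 10%: 0.4 recorded, P = 0.99^40 = 67%
- c = 30%: 1.2 recorded, P = 0.97^40 = 30%
- c = 50%: 2.0 recorded, P = 0.95^40 = 13%
- c = 90% (assumed for a direct question): 3.6 recorded, P = 0.91^40 = 2%

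Over p = 5% to 20%, P runs from 55% down to 8% at c = 30%, and from 16% to under 0.1% at c = 90%. This shows only that an empty arm can be compatible with several events when reporting is voluntary. It does not estimate the under-recording.

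**The case against.** The best case for the plan has four parts.

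**The text does not call this the sole route.** It says what happens if the team learns of harm, and a fuller protocol could hold more procedures. This carries some weight. But the article goes beyond silence: it states a capture rule and presents its instrument table as listing all outcomes and instruments. No item described elsewhere in the article fills the gap.

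**Other signals exist.** Consent information names a contact, and each session email invites participants to raise technical difficulties or other obstacles with the software. Attrition is compared by arm, and reasons for missing data will be reported. These stand as partial mitigation. None of them asks about harm, and the email route is started by the participant and framed around the software.

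**Risk is minimal and safety is not claimed.** The task is about 15 minutes of keyboard responses, two ethics committees approved it, and no aim or hypothesis concerns safety. This stands, and it sets the priority low.

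**The remedy is imperfect.** One open question recalled over weeks will miss some brief, mild reactions. That is true, but it is still better than no question.

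Two stronger readings are tempting. A reader might infer that the 7-day recall of the PROMIS forms makes them defective because they cannot reach the early sessions. The document does not support treating this as a fault: the forms were chosen as efficacy outcomes, not as safety instruments, and one pain-intensity item asks about pain at the moment of answering. A reader might also infer that harms would go wholly unseen. The six rows counted above, together with attrition and reasons for missing data, show otherwise.

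**Conclusion.** The point holds in a limited form. Recording depends on the team becoming aware, nobody is present to notice, and 0 of 15 post-exposure rows ask about unwanted effects. Effects other than lasting change in pain, interference, anxiety or depression will therefore probably be under-recorded. That is an inference from the design. It assumes that participants volunteer fewer effects than they would report if asked, and that no solicited item exists outside the table.

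The size cannot be derived from the document. No stated figure is wrong and no efficacy result changes. Given the low risk, this is worth doing because it is cheap, not because the trial is unsound without it. Nor does the document give reason to have adverse events tabulated by arm during the trial; at this level of risk, pooled review is enough.

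**What to change.** - Add one open question on unwanted effects to the posttraining and 1-month surveys. Use the recall window of the existing pain-treatment question (from study start, or from the previous assessment), so that the two surveys together cover the whole period from the first session.
- Have the team review the answers, pooled over arms, at its regular meetings, and report them by arm at the end.
- Send the posttraining survey to all randomised participants at the end of the 3-week period, not only on completion of session 6. This matches the follow-up intention in Statistical Methods and reaches those who stop early.
- Report separately the participants who finished before the question was added.

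Cost: one item in two existing surveys, one changed invitation trigger and an ethics amendment. No efficacy data are examined early and no alpha is spent. The downsides are more reports of minor effects such as fatigue and, because recruitment began in August 2021, an incomplete harms record for earlier finishers.

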### Sample Size Estimation

To the best of our knowledge, there are no similar published studies on gamified pain ABMT or ABMT for adults with chronic pain that directly compare 3 groups (ie, control ABMT, standard ABMT, and gamified ABMT); therefore, there is no previous effect size on which to base a sample size estimation. As such, a minimum sample size of 30 per training group is planned on the basis that this exceeds the sample size determined by several similar pain ABMT and gamified training studies [7,10,80]. Sharpe et al [7] determined that a sample size of 12 per group was enough to achieve 82% power with a significance level of .05 for their study of ABMT in adults with chronic pain that compared 2 groups (ABMT vs placebo), for which a medium effect size (Cohen *d*=0.45) on pain interference was found in the intervention group (ABMT: n=22; placebo: n=12). Heathcote et al [10] determined a sample size of 20 per group for their study of ABMT in adolescents with chronic pain that compared 3 groups (ie, ABMT, placebo, and waitlist). Boendermaker et al [80] observed in their study, which involved a sample size of <20 per group, that gamified cognitive bias modification training (for alcohol problems) had a positive impact on motivation to train compared with regular training. Considering attrition rates of previous trials in chronic pain treatment [81] and given the 1-month follow-up measurement, a dropout rate of approximately 30% is expected for the current trial. Therefore, a total target sample size of 120 participants (40 participants per group) will be sought. To help achieve adequate participant enrollment, we developed engaging recruitment materials and selected multiple channels for delivery.

### Statistical Methods

#### Overview

Statistical analyses will be conducted after data collection is completed using the SPSS version 27.0 or later (IBM Corp). Continuous data will be presented as means and SDs, whereas categorical data will be presented as frequencies and percentages. Analyses will follow the intention-to-treat principle and will include all randomized participants who successfully complete at least one training session (ie, minimum threshold exposure to ABMT). To determine whether there are any pretraining differences between the training conditions on demographic variables and baseline characteristics, a series of analyses will be performed. The rates of and reasons for missing data will be reported. To manage missing data, the study will attempt to follow-up on all randomized participants (even if they withdraw from the trial) and, where appropriate, use multilevel modeling for repeated measure data analyses as it allows the incorporation of all available data. Significance for all statistical tests will be set at *P*<.05 (2-tailed). Effect sizes will be presented by its most appropriate effect size (and 95% CI), as described by Lakens [82], with a preference for Cohen *d* where possible [83]. No interim analyses of the trial outcome data are planned.

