**Methods:**

A total of 120 adults with chronic musculoskeletal pain, recruited from clinical (hospital outpatient waiting list) and nonclinical (wider community) settings, will be included in this randomized, double-blind, placebo-controlled, 3-arm trial. Participants will be randomly assigned to complete 6 web-based sessions of dot-probe nongamified sham control ABMT, nongamified standard ABMT, or gamified ABMT across a period of 3 weeks. Active ABMT conditions will aim to train attention away from pain-relevant words. Participant outcomes will be assessed at pretraining, during training, immediately after training, and at the 1-month follow-up. Primary outcomes include pain intensity, pain interference, and behavioral and self-reported engagement. Secondary outcomes include attentional bias for pain, anxiety, depression, interpretation bias for pain, and perceived improvement.

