### Aims and Hypotheses

The aim of this study is to investigate the effects of a gamified web-delivered ABMT intervention in a sample of adults with chronic musculoskeletal pain via a randomized, double-blind, placebo-controlled trial. To do this, 3 ABMT conditions will be directly compared: nongamified sham control ABMT, nongamified standard ABMT, and gamified ABMT. It is hypothesized that the gamified ABMT condition, relative to both the standard ABMT and control ABMT conditions, will rate more highly on self-reported engagement (ie, task-related engagement, enjoyment, and interest) as well as complete more training sessions and have less dropout. On the basis of the findings from the broader ABMT literature and theoretical considerations [20-22], it is expected that the standard ABMT and gamified ABMT conditions will show a reduction in pain-related attentional biases and interpretation biases after training sessions, with the largest reduction in the gamified ABMT condition. Furthermore, it is expected that both the standard ABMT and gamified ABMT conditions, relative to the control ABMT condition, will show reductions in pain intensity, pain interference, anxiety, and depression scores immediately after training and 1-month later and that these reductions will be greater in the gamified ABMT condition compared with the standard ABMT condition. Finally, it is expected that both the standard ABMT and gamified ABMT conditions, relative to the control ABMT condition, will report global pain-related improvements following training and that these improvements will be larger in the gamified ABMT condition compared with the standard ABMT condition.

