##### Engagement

Participants’ experiences of engagement will be assessed using 2 self-report measures. Task-related engagement will be measured after each training session with a single-item question: *How engaging was this session?* The item is rated on a 10-point Likert scale, ranging from 1 (*not at all*) to 10 (*very much*), with a higher score indicating greater engagement. Task-related interest and enjoyment will be assessed using the Intrinsic Motivation Inventory—Interest and Enjoyment subscale [56-58]. The subscale comprises 7 items, which are scored on a 7-point Likert scale ranging from 1 (*not at all*) to 7 (*very true*), with higher scores representing higher levels of interest and enjoyment. The reliability and validity of this subscale have been established in previous research [59,60].

Nonuse intervention attrition [61] (ie, the proportion of participants who discontinue using the intervention at each training session) and completion rates (ie, the proportion of sessions, out of 6, that each participant completes during the training period) will be used as objective behavioral measures of engagement.

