##### Validity Check

As recommended by Oppenheimer et al [78], instructional questions will be included in the pre- and posttraining surveys (eg, please select *5=Always*) to identify careless responding patterns. Participants will be excluded if they answer all instructional questions incorrectly.

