#### Engagement Measures

To examine changes in task-related engagement in different training conditions, a multilevel modeling analysis will be conducted. The time point (level 1 units) will be nested within participants (level 2 units). The variable time will have 6 levels (ie, after sessions 1, 2, 3, 4, 5, and 6). A model-building procedure [84] will be used to build the most parsimonious model to test the hypotheses, using the AIC to identify the most appropriate model. The model will be computed using maximum likelihood estimation. To analyze the impact of gamification on interest and enjoyment, a 1-way analysis of variance will be performed. Missing values will be handled using multiple imputations.

Regarding behavioral engagement, Kaplan-Meier survival curves [85] will be calculated to assess the time at which attrition occurred in each training condition and compared statistically using a log-rank test. Participants will be classified as noncompleters if they do not complete all 6 training sessions. Finally, a 1-way analysis of variance will be performed to determine whether there are differences in the mean number of sessions completed between the training conditions.

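### The set called intention-to-treat leaves out randomised participants who complete no session, so the primary attrition and sessions-completed analyses cannot count them

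*Protocol article*

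**What the plan says.** The Overview under Statistical Methods invokes intention to treat and in the same sentence says that the analyses "will include all randomized participants who successfully complete at least one training session (ie, minimum threshold exposure to ABMT". The Procedure section puts allocation before any training, directly after the baseline survey: "Participants will then be randomized into 1 of the 3 groups and be invited by email to start their first training session".

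The abstract lists the primary outcomes: "Primary outcomes include pain intensity, pain interference, and behavioral and self-reported engagement". Under Aims and Hypotheses, the gamified arm is expected to "complete more training sessions and have less dropout" than both other arms. The Engagement section defines attrition as "the proportion of participants who discontinue using the intervention at each training session", and completion as each person's share of the 6 sessions.

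Under Engagement Measures, anyone who does not finish all 6 sessions is a noncompleter. Time to attrition is compared by Kaplan-Meier curves and a log-rank test, and a one-way analysis of variance tests for "differences in the mean number of sessions completed between the training conditions". Neither analysis is given a population of its own.

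**The concern.** Completing a session happens after randomisation, so requiring it for entry is not intention to treat. The set is a modified one under the wrong label.

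For most outcomes this would be a familiar weakness. Here it reaches further, because the entry condition is part of a primary outcome. A randomised person with no completed session is a noncompleter under Engagement Measures. If there is no response to four sessions and four reminders, that person is also a dropout under the Overview of Study Program. This is the worst value the endpoint can take, and the rule deletes it.

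The loss may also depend on arm. Someone who starts the training part of session 1 and abandons it has met either the plain task or the game elements. The Gamified ABMT section sets the game goal at the start, gives emoticon feedback during practice and shows fireworks after the first block. Having not completed a session, that person leaves the analysis. What is at stake is an unbiased test of whether gamification improves retention.

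**Working it through.** The article gives no figure for the number who fail to complete session 1, so there is nothing to reproduce. What follows is the algebra of the rule, then illustrations on assumed counts.

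**From the article:** n = 40 randomised per arm and about 30% expected dropout, not split by session (Sample Size Estimation); 6 sessions (Procedure).

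**Notation, per arm:** D = all noncompleters; s = those among them who do not complete session 1.

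- Dropout among all randomised: D/n.
- Dropout in the planned set: (D − s)/(n − s). This is lower whenever s > 0 and D < n.
- Zero-session participants add nothing to the total of sessions, so the mean in the planned set equals the mean among all randomised × n/(n − s). It is higher whenever s > 0.

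**Illustration 1: fixed totals, varying split.** Assume D = 12 (standard) and D = 6 (gamified). The true difference is 12/40 − 6/40 = 30.0% − 15.0% = 15.0 points.

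| Session 1 losses, standard vs gamified | Standard, planned set | Gamified, planned set | Difference |
|---|---|---|---|
| 4 vs 1 | 8/36 = 22.2% | 5/39 = 12.8% | 9.4 points |
| 4 vs 2 | 8/36 = 22.2% | 4/38 = 10.5% | 11.7 points |
| 3 vs 3 | 9/37 = 24.3% | 3/37 = 8.1% | 16.2 points |
| 1 vs 4 (mirror of the first row) | 11/39 = 28.2% | 2/36 = 5.6% | 22.6 points |

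The contrast shrinks in the first two rows and grows in the last two. With equal losses s it is multiplied by 40/(40 − s), here 40/37. Larger distortions arise when s differs by arm.

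**Illustration 2: same later dropout in both arms.** Assume that 20% of those who complete session 1 stop later, after a mean of 3 sessions. The planned set then always shows 20% dropout and a mean of 0.2 × 3 + 0.8 × 6 = 5.40 sessions. Among all randomised, dropout is (s + 0.2 × (40 − s))/40 and the mean is 5.40 × (40 − s)/40.

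| Session 1 losses, standard vs gamified | Dropout, all randomised | Mean sessions, all randomised | Planned set, both arms |
|---|---|---|---|
| 4 vs 4 | 28% vs 28% | 4.86 vs 4.86 | 20%; 5.40 |
| 6 vs 2 | 32% vs 24% | 4.59 vs 5.13 | 20%; 5.40 |

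In the first row the contrast is right but both levels are wrong. In the second row, a real difference of 8 points and 5.13 − 4.59 = 0.54 sessions disappears.

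**The case against.** The restriction is stated openly and a reason is given, namely minimum exposure to the training. It suits the per-session engagement rating, which exists only after a session. That stands for that measure. It does not carry over to attrition and completion, where zero sessions is a valid value.

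Much of the loss at session 1 may be unrelated to arm. Some people will never open the link or install the software, and participants are not told of the three conditions. Session 1 is longer because it includes cognitive assessments (Procedure), and these are not described as differing by arm. This stands, and it limits how far the contrast is likely to be distorted. It leaves two things: the levels are still wrong when losses are equal, and those who quit during the training part have seen their arm's task.

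A reader might infer more than the article supports:

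- **That the rule works against gamification.** This presumes that gamification reduces quitting in session 1, which is part of what the trial tests. If gamified participants quit more in session 1, the rule hides that instead.
- **That a particular share of the effect is lost.** The 4 vs 1 split would suggest more than a third, but no split has a basis in the article. The expected 30% is overall dropout, set with the 1-month follow-up in mind, and not a rate of session noncompletion.
- **That the randomised comparison of pain outcomes is broken.** People with only a baseline value add little on change to a maximum likelihood multilevel model. The posttraining invitation follows the final session, so zero-session participants would mostly add a 1-month value, if any. The effect is unquantified and probably small.
- **That the careless-responding rule is a second fault of the same kind.** It reads "Participants will be excluded if they answer all instructional questions incorrectly", and such questions appear in both the pre- and posttraining surveys. On the natural reading, one correct baseline answer protects a participant. It is a narrow, separate rule.

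**Conclusion.** The point holds for the analysis population of the behavioural-engagement outcomes. The label contradicts the rule attached to it. As written, the rule removes from a primary outcome the participants with its most extreme value.

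Two consequences follow whenever at least one randomised participant completes no session: dropout is understated and mean sessions completed is overstated. A third is conditional: the between-arm contrast can be distorted in either direction, chiefly if quitting in session 1 differs by arm. Its size cannot be stated. The range of 9.4 to 22.6 points against a true 15 rests wholly on assumed totals and splits.

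The conclusion also assumes that the general population rule governs the log-rank test and the analysis of variance, as the article names no other.

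**What to change.** 1. Analyse attrition (Kaplan-Meier and log-rank) and sessions completed in all randomised participants, in the arm assigned. Count a participant with no completed session as an event at session 1 and as 0 of 6 sessions.
2. In the symptom models, include every randomised participant with any available data. The pain, anxiety and depression baselines are collected before allocation, and the Overview of Statistical Methods already promises an attempt to follow up everyone randomised.
3. Keep the at-least-one-session set under the name modified intention-to-treat, as a sensitivity analysis and for the per-session engagement ratings.
4. Report, by arm, how many randomised participants complete no session, separating those who never opened session 1 from those who abandoned it if the software records this.

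The cost of items 1 to 3 is a change of wording, recorded through the route for protocol modifications under Ethics and Dissemination. Task data are saved automatically at the end of each session, so the number of completed sessions is known for everyone randomised and needs no imputation. No interim analysis is planned and analysis follows data collection, so the change can be made before results are seen. The downside is that engagement figures may look slightly less favourable overall.
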